### Secondary outcome measure

#### Perceived justice

Perceived justice will be measured by the organizational justice questionnaire developed and validated by Colquitt [33]. This questionnaire consists of four subscales: procedural justice (seven items with respect to the 'procedures to come to your compensation'), distributive justice (four items with respect to 'your compensation'; this subscale is only questioned when the participant has indicated that the claim is settled), interactional justice (four items concerning 'your lawyer'), and informational justice (five items concerning 'your lawyer'). In total, twenty items will be questioned with five option answer categories (1 = not at all, 5 = always). We applied a Dutch translation by Van Prooijen [34] of the procedural- (α = 0.74), distributive-, and interactional justice scale (not reported in the article) to our target population. We did not find a Dutch translation of the informational justice scale, so we translated the informational justice scale in line with the other scales. Additionally, the interactional justice subscale is applied to 'the opposite party'.

#### Burden

Participants will indicate to what extent they considered the claims settlement process to be a burden on a ten point scale (1 = not at all, 10 = very much).

#### Well-being

Well-being will be measured by 1) three subscales of the SCL-90 [35] (i.e. depression, anxiety, and somatization: 38 items), with a five point answer scale (1 = not at all, 5 = very much), and 2) the EQ-5D [36], which is a validated tool for measuring quality of life. It consists of i) five items (mobility, self-care, usual activities, pain/discomfort, and anxiety/depression) with a three point answer scale (no problems, some problems, or extreme problems) and ii) a visual analogue scale questioning the respondent's self-rated health (0 = worst imaginable health state, 100 = best imaginable health state).

#### Work ability

Work ability will be administered by the first three items of the Dutch version of the Work Ability Index [37], determining individual work capacity. Work is defined as a paid job, but also studies, housekeeping, care for fellow human beings, and volunteer aid. The first question asks subjects to rate their current work ability compared to their lifetime best on an eleven point scale (0 = completely unable to work, 10 = work ability at it best). The second and third question ask participants to judge their current work ability considering respectively the physical - and the mental demands of their work (1 = very bad, 5 = very good).

#### Knowledge of claims settlement

Knowledge of claims settlement will be measured by a self developed questionnaire with six items, covering the different components of the information module of the intervention. Participants are asked to what extent they know: 1) the state of affairs regarding the settlement of their claim, 2) what to expect of the claims settlement procedure, 3) what to expect from their lawyer, 4) what to expect from the opposite party, 5) which social services to count on, and 6) what to do in case of conflict. The questionnaire has a five point answer scale (1 = not at all, 5 = a lot).

#### Compensation

Participants will be asked to estimate the amount of compensation they expect to receive. In case the claim is settled, they are asked to fill in the amount of compensation they have received.

#### R-C Communication

The lawyer will be asked to rate the communication with the client (participant) on a scale from 1 to l0.

### Other variables

#### Demographic variables

Demographic variables are: 1) gender, 2) birth date, 3) place of residence, 4) country of birth, 5) educational level (five answer options), and 6) whether the respondent had a paid job at the time of the accident (employer, self-employed, or unemployed).

#### Accident

Questions concerning the accident are: 1) participant's means of transport when the accident happened (motorized or not motorized), 2) date of accident, and 3) the extent in which the offender can be blamed for the accident (1 = not at all, 5 = very much).

#### Injury

Injury details will be measured by questioning: 1) what body part is injured (a) shoulder, arm or hand, b) head or neck, c) hip, leg or foot, d) trunk or back; multiple answers possible), 2) whether one was admitted to the hospital (if yes, how many days), and 3) whether the injury can be objectified (e.g. by scan).

#### Claims settlement

Claims settlement details are: 1) date of first contact with lawyer, 2) name of lawyer, and 3) name of opposite party.

#### Website satisfaction

Website satisfaction will be measured by one question asking to rate the website on a scale from 1 to10.

#### Website usage

Website usage is the amount of webpage views, which is automatically registered in the *back office *of the website.

An overview of measurements is displayed in table 1.

**Table 1 T1:** Schedule of measurements

Measurement		T0	T1	T2	T3
		Baseline	3 months	6 months	12 months
Empowerment	Mastery scale	7	7	7	7

Self efficacy	Self developed items	9	9	9	9

Justice	Organizational justice	20	20	20	20
	
	Self developed items	4	4	4	4

Burden	Self developed item	1	1	1	1

Well being	SCL-90 (3 subscales)	38	38	38	38
	
	EQ-5D	6	6	6	6

Work ability	Work ability index	3	3	3	3

Knowledge	Self developed items	6	6	6	6

Compensation claim	Self developed item	-	-	-	1

R-C communication	Self developed item	-	-	-	1

Demographics	Self developed items	6	-	-	-

Accident	Self developed items	3	-	-	-

Injury	Self developed items	3	-	-	-

Claims settlement	Self developed items	3	-	-	-

Website satisfaction	Self developed item	-	-	-	1

Website usage		Number of webpage views			

**Total number of questions**		**109**	**94**	**94**	**97**

### Statistical analysis

Descriptive statistics (categorical and continuous variables) will be analyzed by respectively chi-square and t-test. All analyses will be conducted according to the intention-to-treat principle. Missing values will be imputed with regression imputation techniques. Differences between the intervention group and control group will be evaluated by two tailed tests at significance level of 5% (p < 0.05). Short term (T1, T2) and long term (T3) effects will be analyzed by a repeated measure analysis. Finally, the results of the intention-to-treat analyses will be compared to the results of the per-protocol analyses.

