### Sample size

The primary outcome variable of this study is empowerment, which is measured by the Mastery Scale [28]. This scale has a range of 7 to 35. To be able to show a medium effect size (Cohen's d of 0.50) using a power of 80% and a two-sided alpha of 5%, we will need 63 participants per group. Taking into account a loss to follow-up of 25%, we will need to randomize 85 participants per group. Having two groups (intervention group and control group), a total of 170 participants is needed.

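### Read as single imputation, the stated regression imputation either understates the standard errors or shrinks the treatment effect at the planned 25% loss

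*Protocol article*

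**What the plan says.** The Statistical analysis section of the protocol article handles missing data in one sentence: "Missing values will be imputed with regression imputation techniques". The sentence before it reads "All analyses will be conducted according to the intention-to-treat principle". The completed data then go into two-sided tests at 5% and a repeated-measures analysis of T1 and T2 (short term) and T3 (long term). The section does not mention several imputed data sets, pooling, a variance correction or the variables in the imputation model. The only other analysis named is a per-protocol comparison.

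The Sample size section expects substantial loss: "Taking into account a loss to follow-up of 25%, we will need to randomize 85 participants per group". It gives no breakdown of that loss by visit.

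**The concern.** In ordinary use, regression imputation means that each gap is filled once with a value predicted from a regression, and the later analysis treats that value as if it had been measured. With 25% loss, about 85 × 0.75 = 63.75 participants per arm have an outcome, yet the test counts 85.

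What follows depends on a choice that the article does not state:

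- **Arm in the imputation model.** The estimate is unbiased, but the standard error is too small and the nominal 5% test rejects too often.
- **Arm left out.** Imputed participants carry little or none of the treatment effect, so the estimate is pulled toward zero.

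The first case matters for the trial's conclusion. Under the Self-efficacy heading, empowerment is declared improved if one of the two scales is positive and the other is not negative. Inflated error on either scale therefore passes into the main claim. The per-protocol comparison does not correct standard errors that come from imputed data.

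**Working it through.** **Inputs from the article.** Effect 0.50 SD, power 80%, two-sided 5%, 63 evaluable and 85 randomised per group, 25% loss, follow-up at T1, T2 and T3.

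**Assumptions (not in the article).** Values are missing completely at random. The within-person correlation is 0.3 to 0.7. Dropout follows one of the patterns in step 4.

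**1. The plan's own figure.** n per group = 2 × (1.96 + 0.84)² / 0.50² ≈ 62.7, so 63, which agrees with "using a power of 80% and a two-sided alpha of 5%, we will need 63 participants per group". Dividing by 0.75 gives 63 / 0.75 = 84, against 85 stated. The sample size reproduces and is not in question.

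**2. Approximate algebra for one follow-up.**

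- *Single prediction, arm included.* Imputed values have zero residual, so the residual variance is understated by a factor of 0.75, and it is divided by 85 instead of 63.75. Reported / true variance = 0.75 × (63.75 / 85) = 0.5625. The SE ratio is √0.5625 = 0.75. Type I error = 2 × (1 − Φ(1.96 × 0.75)) = 2 × (1 − Φ(1.47)) = 14.2%.
- *Single draw with a random residual, arm included.* Reported variance is proportional to 1/85 = 0.01176. True variance is proportional to 1/63.75 + 0.25/85 = 0.01569 + 0.00294 = 0.01863. The SE ratio is √(0.01176 / 0.01863) ≈ 0.795. Type I error = 2 × (1 − Φ(1.56)) ≈ 12%.
- *Arm omitted, prediction from T0 only.* Expected estimate = 0.50 × (1 − 0.25) = 0.375.

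**3. Simulation, one follow-up.** 85 per arm, 25% missing, baseline-adjusted ANCOVA, 2,500 trials per setting; ranges are over correlations 0.3, 0.5 and 0.7.

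| Method | Mean estimate (true 0.50) | Reported SE / true SE | Type I error |
|---|---|---|---|
| Single prediction, arm in | 0.50 | 0.73–0.76 | 13.6–15.4% |
| Single random draw, arm in | 0.50 | 0.77–0.80 | 11.4–13.1% |
| Single prediction, arm out | about 0.37 | 0.98–1.01 | 4.4–5.8% |
| Single random draw, arm out | about 0.37 | 0.98–1.01 | 4.7–5.2% |
| Observed cases only | 0.50 | 0.98–1.02 | 4.4–5.7% |
| Multiple imputation (20 sets), arm in | 0.50 | 0.99–1.02 | 4.4–5.8% |

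**4. Simulation, three follow-ups, as planned.** 85 per arm, equal correlation between visits, each visit imputed once from T0 and earlier visits, then baseline-adjusted tests of T3 and of the T1–T3 mean; 3,000 to 4,000 trials per setting. Type I errors are for single prediction with arm in the model.

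| Dropout pattern | Type I error at T3 | Type I error, T1–T3 mean | Estimate with arm omitted (true 0.50) |
|---|---|---|---|
| 25% lost before T1 | 14.0–14.7% | 13.7–14.8% | 0.37–0.38 |
| Gradual loss, reaching 25% at T3 | about 11–14% | 8.8–10.2% | 0.40–0.44 |
| 25% missing at T3 only | about 11–13% | 5.7–6.1% | 0.47–0.49 (T1–T3 mean) |

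Attenuation is milder with later dropout because fewer visits are imputed and the observed earlier visits carry part of the effect into the prediction. With arm omitted, type I error was about 4–6%.

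**The case against.** **The phrase does not say single imputation.** This stands in part. The article speaks of techniques in the plural, and multiple imputation can also be built on regressions. Imputation models and pooling rules are details that a condensed article may leave to a fuller plan. A reader might infer that the primary p-value and confidence interval are simply wrong; the article does not support that without the condition that single imputation is meant. But the sentence names a method, that is the method's usual meaning, and nothing in the article points to multiple imputation.

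**One follow-up with 25% missing is the worst case for an averaged effect.** This stands. The article gives only an overall loss, and if dropout falls at T3 alone the T1–T3 average is tested at about 6%. The T3 test, which carries the long-term claim, remains inflated in every pattern tried.

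**The 5% test is not lost in both cases.** This also stands. A reader might infer that type I error fails whichever way arm is handled. With arm left out it stays near 5%, and the fault is in the size of the estimate.

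**Distributive justice.** A reader might infer that scores would be invented for participants whose claim is still open. The Perceived justice section says that "this subscale is only questioned when the participant has indicated that the claim is settled". An item that was never asked is most naturally not applicable, and the article nowhere counts it as a missing value. No finding rests on this.

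**A mixed model is one acceptable choice among several.** Agreed. Properly specified multiple imputation serves equally well, so both are offered.

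**Conclusion.** The concern holds, on condition that single imputation is meant. As written, the rule then does not deliver both a 5% test and an unbiased effect at the plan's own 25% loss.

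- **Arm in the imputation model:** type I error is about 11–15% at T3 and about 6–15% for the T1–T3 average.
- **Arm left out:** type I error is near 5%, but a true 0.50 SD is estimated as about 0.37–0.49 SD.

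These figures assume values missing completely at random, a within-person correlation of 0.3 to 0.7 and equal correlation between visits. None of these is given in the article. The spread mainly reflects the timing of dropout, which is also not given. If regression-based multiple imputation was intended, the defect lies in the wording alone, but the sentence still needs changing.

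**What to change.** Replace the imputation sentence with one of two statements:

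- The primary analysis is a likelihood-based linear mixed model using all available T1–T3 data of all randomised participants, with no imputation of outcomes.
- Missing outcomes are handled by multiple imputation with arm, accident-age stratum, T0 score and the other visits in the imputation model, and results are pooled by Rubin's rules.

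The cost is one sentence and standard software. The planned 170 participants do not change. Confidence intervals will be wider than single imputation would report. For example, at correlation 0.5 with one follow-up, the true SE is 0.152 SD against a reported 0.115 SD with arm in the model, a factor of 0.152 / 0.115 ≈ 1.32. That extra width is uncertainty that single imputation hides.

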## Discussion

This study is the first to empower PI victims with respect to the negative aspects of the claims settlement process by means of a internet intervention. Below, we will discuss the strengths and limitations of this study.

From a scientific point of view, the results will give more insight into the impact of compensation proceedings on health over time and the phenomena of secondary gain and secondary victimization. Because this study is the first internet intervention applied to legal practice, the study will provide interesting data whether a self-help intervention is applicable to our target population. Furthermore, the website usage data will reveal what kind of PI victims will use which modules and how often.

If we succeed in improving health of PI victims, the results of this study can have important consequences for legal claims settlement. If this research shows that empowerment via an interactive website has a positive influence on the well-being and health of PI victims, than our website has a clear potential to become standard service in legal practice, and possibly even an obligatory service to PI victims, considering the fundamental rule in law that recovery has priority over monetary compensation (*restitutio in integrum*). A positive outcome would constitute the empirical basis for the development of legal rules that would make legal professionals to adhere a more victim-friendly and recovery oriented way of settling PI claims. A further step could be the development of comparable websites, designed to empower individual citizens who are entangled in comparable burdensome legal procedures, e.g. in the field of labor law, housing law, consumer law, administrative law, and civil law in general. Furthermore, the intervention and the results of the study will also be interesting for victimology and criminology studies.

Offering a self-help intervention by which PI victims can keep up with what is going on during the claims settlement process and by which they can learn to cope with problems and worries, could be a promising alternative approach for a problem that until now is only being encountered by educating the legal professionals on more client friendly claims settlement processes.

Another strength of this study is that the intervention is offered through the internet. Hence, the intervention can be accessed easily, at home, and at any time, which is especially advantageous for our target population that is disabled and often immobile. Furthermore, because of the internet, we are able to reach a large audience at low costs, and anonymously, which is beneficial considering the fact that we are providing a service for a hardly acknowledged health problem.

The fact that we choose to recruit participants via only one claims settlement office has both advantages and disadvantages. The first advantage of recruitment via a claims settlement office (compared to indirect recruitment via the media) is that we assume to have a relative smooth inclusion of participants, because we can directly approach a large number of PI victims. Second, we assume that lawyers working in the same claims settlement office have a similar method of claims settlement, so that 'method of claims settlement variability' will not be a confounder. However, recruitment via only one office also implies two possible selection biases. First, it might be that the characteristics of clients of this particular claims settlement office may differ from clients of other offices. Second, this claims settlement office is one of the first offices in the Netherlands which offers their clients online access to their claims settlement dossier, a service which will be a standard service in the future, but at the moment is not usual care.

A limitation of the study is that the claims settlement process will be different for all participants: different length, different steps, different pace, and different problems. Because of this variability, we cannot investigate whether there are moderating factors influencing the study outcomes. Furthermore, some of the claims will be settled before the end of the study. Participants whose claim is already settled early in the study, will use the intervention for a short time only and their reports will be influenced by the perceived fairness of the compensation they received (distributive justice), so they need to be analyzed differently. However, it is unclear whether the number of settled claims will be large enough to draw conclusions about this subgroup.

A second limitation concerns the generalization of the study results. Because our participants are traffic accident victims, further research is needed to find out whether the results can be generalized to other kinds of PI victims, such as victims of medical malpractice, workplace accidents, and violent assaults. Furthermore, because of international variety in compensation proceedings and legal services delivery [38], we should be careful to generalize the study results to countries with different ways of claims settlement processes. General tort law might give different needs and experiences than a no-fault system. The same goes for claims that are settled out of court versus claim proceedings in court, or PI victims who are represented by a lawyer compared to PI victims who are not represented by a lawyer.

The results of this study are expected in early 2012.
